### Statistical methods

Participant/subject characteristics will be summarized using mean, standard deviation, median and inter-quartile range. Categorical variables will be summarized using frequencies, percentages and 95% confidence intervals. Means will be compared between the Intervention condition and TAU condition using the t-test or Mann-Whitney test. Comparisons of proportions between conditions will be performed using the Chi square test or Fisher’s exact test, as appropriate. Differences in the incidence of subsequent DSH between the Intervention and TAU conditions at 6 and 12 months will be investigated using multi-level negative binomial regression models (individuals nested within hospitals) to estimate the incidence risk ratios (IRR) and absolute risk differences based on incidence proportions in an intention to treat analysis. Adjustment for potential confounders identified from descriptive analyses will also be included in multivariate regression models as appropriate.

Relative differences in time to first subsequent DSH event between Intervention and control conditions at 6 and 12 months will also be investigated using multi-level Cox proportional hazard regression models (individuals nested within hospitals) to estimate hazard ratios (HR), with adjustment for potential confounders as appropriate. Kaplan-Meier survivorship functions and clustered log-rank tests will also be calculated to assess differences between Intervention and TAU conditions, with median time to first DSH event compared for Intervention and TAU conditions.

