### Randomization, allocation, and materials

Participants/subjects will be stratified (first ever hospital-treated DSH verses any subsequent episode), then randomly assigned and enrolled into the study following the Zelen single-consent design [11]. Since there are different repetition rates of DSH for initial and subsequent DSH, participant/subject numbers will initially be stratified by first or subsequent DSH presentation. They will then be randomized within strata, using random permuted blocks of size 6, to either the Intervention or control condition (TAU) using a computer-generated randomization program.

Study materials, including an ‘Allocation Information Sheet,’ will be organized within numbered envelopes, with each hospital having at least two ‘enrolment boxes’ (document drawers) containing a full set of materials. Research staff will confirm that the placement of research materials and the Allocation Information Sheets within envelopes match the randomized numbers generated from the randomization program (to prevent any tampering with the allocation sequence).

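### The primary models leave out the randomisation stratum (first versus subsequent DSH) and take covariates from the trial's own descriptive analyses; the cost is small and the correction is free

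*Protocol article*

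**What the plan says.** Under Randomization, allocation, and materials, the protocol article sets the stratification factor: "Participants/subjects will be stratified (first ever hospital-treated DSH verses any subsequent episode), then randomly assigned". It gives the reason, "Since there are different repetition rates of DSH for initial and subsequent DSH", and the method: "They will then be randomized within strata, using random permuted blocks of size 6". So the document itself treats DSH history as prognostic for the primary outcome.

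Under Statistical methods, the repetition event rate is analysed with "multi-level negative binomial regression models (individuals nested within hospitals"), by intention to treat. Time to first re-presentation is analysed with "multi-level Cox proportional hazard regression models (individuals nested within hospitals) to estimate hazard ratios (HR), with adjustment for potential confounders as appropriate". Log-rank tests are to be clustered. Hospital is the only design factor named in any of the three; first versus subsequent DSH appears in none.

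The covariate rule for the count model is "Adjustment for potential confounders identified from descriptive analyses will also be included in multivariate regression models as appropriate". Earlier in the same paragraph, the only comparisons described before the regression models are between arms: "Means will be compared between the Intervention condition and TAU condition using the t-test or Mann-Whitney test" and "Comparisons of proportions between conditions will be performed using the Chi square test or Fisher’s exact test, as appropriate".

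Under Data collection, the presenting group (first or subsequent DSH) is recorded for each patient.

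**The concern.** Three things do not fit together.

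1. **Design and analysis differ.** Stratified randomisation removes chance imbalance on DSH history, so the treatment estimate varies less from trial to trial than an unstratified analysis assumes. A model without the stratum leaves the between-strata variation in its error term, and its standard error tends to be somewhat too large.
2. **The covariate rule depends on the data.** Covariates are found by looking at the trial's own descriptive results and added where thought appropriate. If the criterion is imbalance between arms, it says nothing about prognostic strength, and it will pass over the variable that the randomisation has already balanced.
3. **The primary result is not designated.** The text provides for models with hospital nesting and for adjustment, but does not say which result answers each hypothesis.

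At stake are a little precision and, more importantly, one clearly identified primary estimate for each endpoint.

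**Working it through.** **The plan's own figure.** The article requires 796 patients (398 per arm) for RR = 0.66, 5% significance, 80% power and a 10% allowance for hospital. It gives no control event rate or dispersion for this endpoint, so 796 cannot be reproduced from stated inputs. The rate formula is n per arm = (z_α + z_β)² × [1/λ + 1/(0.66λ)] / (ln 0.66)², two-sided α assumed. With λ = 0.316 per year:

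- (z_α + z_β)² = 7.849; (ln 0.66)² = 0.1727; bracket = 3.165 + 4.795 = 7.959
- n = 7.849 × 7.959 / 0.1727 = 361.8; × 1.1 = 398.0

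The rate 0.316 is therefore an assumption chosen to match 796, used below only to size the effect of the stratum. Higher rates with overdispersion also match (0.4 per year with dispersion about 0.84).

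**Step 1. Could an arm comparison select the stratum?** A block of 6 holds three patients per arm, so with one sequence per stratum the arms differ by at most 3 within a stratum. Take the worst case: 201 v 198 first-DSH patients and 197 v 200 subsequent-DSH patients.

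- Difference in first-DSH share = 3/398 = 0.0075
- SE = √(2 × 0.25/398) = 0.0354
- z = 0.21, p = 0.83

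Simulation agrees. With 796 patients and first-DSH shares of 30%, 50% and 70%, the stratum was flagged in 0 of 5,000 trials at p < 0.05 and in 0 of 5,000 at p < 0.20. Under simple randomisation the figures were about 5% and 19 to 20%. With six enrolment boxes (assumed two per hospital), each with its own sequence in each stratum, the result was 0 of 3,000 at both thresholds.

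**Step 2. What does leaving the stratum out cost?** Assumptions: mean control rate 0.316 per year, dispersion k = 0.3 within strata, strata 50:50, 398 per arm, no hospital effect, 800 runs per setting.

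| Rate ratio between strata | Power without stratum | Power with stratum | Type I error without | Type I error with |
|---|---|---|---|---|
| 1.5 | 79.7% | 79.9% | 6.0% | 6.0% |
| 2 | 80.2% | 80.6% | 4.9% | 5.6% |
| 3 | 77.5% | 79.4% | 3.9% | 4.5% |

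Monte Carlo error: √(0.8 × 0.2/800) = 1.4 points for power and √(0.05 × 0.95/800) = 0.8 points for type I error.

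**Step 3. Hand check at ratio 3.** The stratum control rates are 2 × 0.316/4 = 0.158 and 3 × 0.158 = 0.474.

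- *Without the stratum.* The squared coefficient of variation of the stratum rates is 0.25, so effective dispersion is 0.3 × 1.25 + 0.25 = 0.625. Variance = (7.959 + 2 × 0.625)/398 = 0.02314; SE = 0.152.
- *With the stratum.* The variances are 0.0830 (low-rate stratum) and 0.0297 (high-rate stratum), from [1/λ + 1/(0.66λ) + 0.6]/199. Pooled variance = 1/(1/0.0830 + 1/0.0297) = 0.0219; SE = 0.148.

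Both match the mean model SEs in the simulation (0.152 and 0.148). The empirical SD of the estimate was 0.144 either way. The difference therefore lies mainly in the reported standard error, with the unstratified model slightly conservative, and not in the estimate.

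**Step 4. Does data-driven selection inflate type I error?** In an illustrative null simulation with nine assumed covariates, taking the better of the unadjusted and imbalance-selected results rejected in 5.3%, against 4.9% for the unadjusted analysis alone. No material inflation was seen.

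**The case against.** The case on the other side is substantial, and much of it stands.

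- **Selection by arm imbalance is not stated.** The text says only descriptive analyses. They could include associations with outcome, which might pick up DSH history, and nothing bars the stratum. This stands, so Step 1 is conditional on the reading. On either reading, however, the covariates are chosen after data are seen.
- **A base estimate may exist.** The word *also* in the covariate sentence can mean adjusted models in addition to the specified one. A reader might infer that no primary estimate exists until the data are seen; the text does not support that. What remains is that it does not say which result is primary. The Cox sentence is less clear still.
- **Arm differences need not be pure chance.** Under Zelen single consent, only Intervention patients are asked for consent, after allocation, and refusers appear among the exclusions. If refusers were dropped, imbalance could be systematic and could reach the stratum. The stated intention-to-treat analysis points the other way; the balance argument assumes that all randomised patients are analysed.
- **A reader might infer that the trial is already under-powered and cannot spare precision.** That would need an event rate and dispersion that the article does not give. Assumed values can be chosen that give about 80% power, as above, or much less. This point does not depend on it.
- **A reader might take the tests of means and proportions to be baseline significance tests.** The text does not say so. Any DSH re-presentation is a secondary endpoint for which a chi-square test is ordinary. No criticism of those tests is made here.
- **A condensed article may leave covariate detail to an analysis plan.** That covers an absent covariate list. It does not cover a rule that the article states and that depends on the data.

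**Conclusion.** The point holds in a limited form. The randomisation uses a factor that the article calls prognostic, the primary analyses as stated do not use it, and the stated covariate rule leaves adjustment to be settled after data are seen, without saying which result is primary.

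The numerical effect is small: about 0 to 2 points of power for assumed rate ratios between strata of 1.5 to 3, differences near or within Monte Carlo error, and at most slight conservatism when the stratum is left out. Neither bias nor type I error inflation was shown. The sizes rest on an assumed event rate, dispersion and 50:50 split, with hospital effects left out of the simulation. The argument for change is agreement between design and analysis and a single designated primary result, not rescue of the trial's validity.

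**What to change.** In Statistical methods:

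1. Include first/subsequent DSH as a fixed covariate in both the negative binomial and the Cox model, keeping individuals nested within hospitals, and declare these models primary.
2. Stratify the planned clustered log-rank test by first/subsequent DSH. Hospital is not stated to be a randomisation stratum, so the planned clustering can stay as it is.
3. Replace the selection of confounders from descriptive analyses with covariates named in advance for their prognostic value, used in sensitivity analyses only.

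The cost is one paragraph of wording. The stratum is already recorded for every patient, and no stated sample size changes.

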## Background

Hospital-treated DSH is common [1] and costly [2]. Repetition of DSH within 1 year of hospital admission occurs at a median proportion of 15% (interquartile range 12–25%) [1].

DSH is associated with a range of psychiatric issues [3], an increased risk of suicide attempts, and suicide [3, 4]. In Australia, DSH accounted for 6% of all hospitalised injury cases during 2012–2013 and four-billion dollars in healthcare expenditure annually, making prevention and early intervention an Australian national health priority [5]. Hospital-treated DSH predominantly includes deliberate self-poisoning (DSP) (approximately 90% of DSH cases) and other various methods, including, cutting, hanging, jumping, and burning [1]. Hospital-treated DSH is associated with an increased risk of suicide death, highlighting the importance of effective prevention and early intervention strategies.

BCIs, such as follow-up postcards, supportive letters, or phone calls have previously been shown to be associated with reductions in hospital re-presentation event rates. A recent systematic review and meta-analysis of BCIs for reducing DSH (letters, telephone calls and crisis “green cards”) found a non-significant benefit for any episode of repeat DSH (binary outcome) and a significant benefit for repetition event rates [6]. The individual studies identified in the systematic review and meta-analysis generally lacked statistical power and varied considerably in intervention timeframes and methodologies, highlighting the need for well-designed, large, RCTs to determine the efficacy of these BCIs.

SMS text messaging provides more immediate communication and may be a more effective intervention than postcards [6, 7]. Text messaging has been associated with positive outcomes for hospital patients in a pilot study [8] and in a prospective study [9]. These studies demonstrated the technical feasibility and acceptability of text messaging outreach in post-acute suicide attempters in different cultural contexts. Most participants considered the text message contacts an acceptable and useful form of help and indicated they wished to continue receiving those text messages.

If an SMS text messaging follow-up intervention is found to be effective in reducing DSH re-presentations, it would provide a lower-cost, higher coverage medical follow-up system than what has previously existed for this population.

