### Outcome measures

As primary endpoints, we will assess at 6 and 12-months post-index discharge, i) the number of hospital DSH re-presentations in each condition (repetition event rate) and ii) the time to first re-presentation in each condition. Secondary end-points include i) any DSH re-presentation, ii) suicide mortality, and iii) all-cause mortality. Mortality data will be obtained from routinely collected data sources available through NSW Health, other government agencies, and the Centre for Health Record Linkage (CheReL).

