### Sample size calculation

Assuming an incidence rate ratio (based on event rates) of RR = 0.66 [13] for the Intervention condition compared to TAU, with a 5% significance level, 80% power, and 10% adjustment for correlation of individuals within hospitals, a total sample size of 796 participants/subjects is required (398 participants in the Intervention condition and 398 subjects in the control condition). We have also assumed a median survival time (time to first repetition) in the TAU condition of 4.3 years. Currently ~ 15% in the usual care group who present for DSH re-present within the following 12-months, or a probability of survival of 0.85. Median survival (m) after 1-year (t) in the usual care group is t*log_e_(1/2)log_e_(*p* = 4.3 years). For assessing differences in median time to first repetition, assuming a median survival time in the usual care group of 73.5 days [12] and a similar relative difference in event rates between Intervention and TAU conditions as above (RR = 0.66), [13] the estimated median survival time in the Intervention condition is 121.8 days, which requires a total sample size of 138 participants/subjects (69 participants in the Intervention condition and 69 subjects in the TAU condition), with 5% significance and 80% power, and 10% adjustment for correlation of individuals within hospitals. The number of patients likely to die within the study period is very small. A previous longitudinal study in a similar Australian hospital setting [12] found a 1% suicide rate after 24 months and nearly a 2% suicide rate after 5 years.

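### The planned comparison of median time to first DSH event is expected to be inestimable: with about 15% re-presenting in 12 months of follow-up, neither arm should reach its Kaplan-Meier median

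*Protocol article*

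**What the plan says.** Outcome measures (Protocol article) names two primary endpoints, assessed at 6 and 12 months after index discharge. The second is "the time to first re-presentation in each condition". Study design fixes follow-up at 12 months.

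For this endpoint, Statistical methods plans multi-level Cox models, Kaplan-Meier functions and clustered log-rank tests, "with median time to first DSH event compared for Intervention and TAU conditions".

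The Sample size calculation gives two incompatible TAU medians:

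- It states "We have also assumed a median survival time (time to first repetition) in the TAU condition of 4.3 years", derived from about "15% in the usual care group who present for DSH re-present within the following 12-months, or a probability of survival of 0.85".
- It then sizes the median comparison separately, at 138 patients, "assuming a median survival time in the usual care group of 73.5 days", and says that "the estimated median survival time in the Intervention condition is 121.8 days".

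**The concern.** A Kaplan-Meier median exists only once the curve falls to 0.50. On the protocol's own rate, the TAU curve stops near 0.85 when follow-up ends. The planned estimate would then come out as not reached in both arms, which leaves nothing to compare.

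This matters because the median is the only summary of this primary endpoint in time units that the article names, and it has its own sample size. If it is not reached, the analysts must improvise after the data are in. The 73.5-day figure makes one improvisation tempting: taking medians among only those patients who re-presented. Membership of that group is itself an outcome of treatment, so the comparison would no longer be between randomised groups. A null result there could be misread as evidence against the second hypothesis even if the intervention works.

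**Working it through.** **Inputs from the protocol.** TAU re-presentation 15% at 12 months; ratio 0.66; 398 per arm; follow-up 12 months; stated medians of 4.3 years, 73.5 days and 121.8 days (all Sample size calculation, except follow-up, from Study design). The upper quartile of published 12-month repetition is 25% (Background).

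**Assumptions.** Constant hazards, as in the protocol's own median formula, and the ratio of 0.66 read as a hazard ratio.

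**1. Reproduce the stated median.** m = t × ln(1/2) / ln(0.85) = 0.6931 / 0.1625 = 4.27 years, which agrees with 4.3.

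**2. Expected survival and medians.** The yearly hazards are 0.1625 (TAU) and 0.66 × 0.1625 = 0.1073 (Intervention).

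| | TAU | Intervention |
|---|---|---|
| Event-free at 6 months | 0.85^0.5 = 0.922 | 0.898^0.5 = 0.948 |
| Event-free at 12 months | 0.850 | 0.85^0.66 = 0.898 |
| Median | 4.3 years | 0.6931 / 0.1073 = 6.5 years |

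**3. Could chance or a higher rate bring the median within reach?**

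- The standard error of TAU survival at 12 months is √(0.85 × 0.15 / 398) = 0.0179, so 0.85 lies (0.85 − 0.50) / 0.0179 ≈ 20 standard errors above 0.50.
- At 25% re-presenting, the TAU median is 0.6931 / 0.2877 = 2.4 years. The binomial probability that at least 199 of 398 re-present is about 8 × 10⁻²⁷.
- Even if early enrollees were observed for 36 months, TAU survival would be 0.85³ = 0.61.

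**4. What the 73.5-day median implies.** The proportion re-presenting by 12 months is 1 − 0.5^(365/73.5) = 96.8% in TAU. For 121.8 days in the Intervention arm it is 1 − 0.5^(365/121.8) = 87.5%. The stated TAU rate is 15%. The size of 138 reproduces only on these short medians: their ratio is 73.5 / 121.8 = 0.603, which needs 124 events by the Schoenfeld formula (two-sided 5%, 80% power), and 124 × 1.10 = 136.4. Allowing for 24 months of accrual plus 12 months of follow-up gives 137.7. At 15% and a ratio of 0.66, the average event probability is (0.150 + 0.102) / 2 = 0.126, so 138 patients would give about 17 events.

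**5. A repeaters-only median, if one were computed.** Among repeaters, the median is the time at which half of the 12-month events have occurred.

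- TAU: ln(1 − 0.075) / ln(0.85) = 0.480 years = 175.1 days.
- Intervention: ln(1 − 0.0509) / (0.66 × ln 0.85) = 0.487 years = 177.6 days.
- Difference: 2.5 days, for a 34% lower hazard.

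In a simulation with 398 per arm under these assumptions, a Mann-Whitney test on repeaters only rejected in 4–5% of trials, which is no more than the significance level. The log-rank test on everyone rejected in about 55%.

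**6. An estimable alternative in time units.** Restricted mean event-free time to 365 days is 365 × (1 − e^(−h)) / h.

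- TAU: 365 × 0.150 / 0.1625 ≈ 337 days.
- Intervention: 365 × 0.1017 / 0.1073 ≈ 346 days.
- Difference: about 9 days. The difference in 12-month event-free proportion is 89.8% − 85.0% = 4.8 points.

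**The case against.** The strongest defence is that the median is one trailing clause. The Cox hazard ratio, Kaplan-Meier functions and clustered log-rank test can all be produced, and the second hypothesis can be tested without any median. This stands. A reader might infer that the time-to-first-event endpoint cannot be analysed, and the document does not support that.

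A reader might also infer that the plan intends a comparison among repeaters. It nowhere says so. Statistical methods attaches the median to the Kaplan-Meier analysis, and the Sample size calculation attributes 73.5 days to the usual care group. That the figure comes from repeaters is a guess prompted by its conflict with 15%. Step 5 therefore describes a risk, not a planned analysis.

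Nor is a repeaters-only median the only one that could be printed. The protocol itself extrapolates to 4.3 years from one-year survival, and a fitted model could do the same in all randomised patients. But an extrapolation to 4–6 years from 12 months of data would rest almost wholly on the assumed model, and the article describes no such model.

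The figures of 175 and 178 days depend on constant hazards. With risk concentrated soon after discharge both would be shorter. The difference would stay small under proportional hazards, but an effect that shifted timing among repeaters could show up.

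Finally, Statistical methods already plans absolute risk differences from incidence proportions at 6 and 12 months, so part of the fix overlaps with existing text. An analysis plan that is not shown may handle an unreached median. The article nevertheless states a comparison that its own assumptions cannot deliver, and that does not depend on any missing detail.

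**Conclusion.** The point holds in a limited form. On the protocol's own figures, the planned comparison of medians is expected to return not reached in both arms at 6 and 12 months: survival of about 0.85 and 0.90 at 12 months, and medians of about 4.3 and 6.5 years. For TAU this rests on the 15% rate and 12-month follow-up and withstands a rate of 25%. The Intervention figures also use the ratio of 0.66 and constant hazards.

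The 73.5-day median cannot describe all randomised TAU patients under the exponential model used in that section. The primary inference from the hazard ratio and log-rank test does not change. What should change is a named summary of a primary endpoint that cannot be delivered, and the opening it leaves for an unplanned substitute.

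**What to change.** In Statistical methods, replace the clause on medians with wording to this effect: in all randomised patients, beside the hazard ratio, report the difference in restricted mean event-free time to 365 days and the Kaplan-Meier event-free proportions at 6 and 12 months with their differences, each with a 95% confidence interval. Report a median only if the curve reaches 0.50. State that no median among repeaters will be compared as a treatment effect.

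In the Sample size calculation, reconcile the two TAU medians, or state which population the 73.5 days describes.

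The cost is a sentence or two of analysis wording and one clarification. It needs no extra patients, visits or data, because the dates of re-presentation are already needed for the Cox model. Part of the event-free comparison coincides with the incidence-proportion differences already planned.
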